#### 4.1.2. Exercise + Sham Neuromodulation Protocol

In the sham group, a needle with a retractable handle, often utilized in experimental research alongside Streitberger and Kleinhenz placebo needles, will be used. These needles mimic insertion without piercing the skin and can remain in place for the duration of the intervention [36]. The design features a retractable mechanism that pulls the needle back into the handle when pressure is applied, creating the appearance of insertion (Figure 4). This arrangement allows the placebo needle to be swapped with a standard needle, preventing patients from visually distinguishing them. To ensure complete blinding of the treatment, patients will be placed in a lateral decubitus position to block their view of the procedure, preventing them from noticing the differences between the sham and intervention groups. Additional steps will include the use of antiseptic solutions and discarding the needles in visible waste containers to enhance the credibility of the procedure. These measures are consistent with the fundamental placebo principles for masking techniques, as described by Braithwaite et al., 2019 [36].

#### 4.1.3. Conventional Physiotherapy

The control group will undergo a conventional pelvic floor therapy program, primarily focusing on Kegel exercises. This structured regimen includes 8–12 individualized sessions, each lasting between 20 and 40 min and conducted twice per week. The therapy emphasizes precise pelvic floor muscle contractions, ensuring that participants activate these muscles independently without engaging the surrounding areas, such as the abdomen, thighs, or glutes [37]. Unlike the intervention group, which engages in more complex full-body exercises aimed at eliciting higher-level corticospinal responses, this approach excludes strength training and broad movement patterns. Additionally, manual therapy techniques will be employed to relieve trigger points in the pelvic muscles and ligamentous structures, incorporating intracavitary methods to address the mechanical pain.

## 5. Patient-Reported Outcome Measures

### 5.1. Anthropometric Variables

Various assessments and studies concerning body sizes and ratios will be carried out. Information will be gathered on factors such as age, sex, weight, height, job, and the date when the initial diagnosis was made. Furthermore, the overall health condition will be documented to detect any possible comorbidities, along with the educational background of each individual. Patients will also need to disclose whether they are using hormone replacement therapy [26].

### 5.2. Primary Outcome

#### The Overactive Bladder Questionnaire-Short Form (OAB-q SF)

The OAB-q SF is a concise, self-administered instrument featuring two scales that evaluate symptom distress and health-related quality of life (HRQoL) in individuals with overactive bladder [38,39]. This condition-specific questionnaire assesses symptom distress using 6 items and health-related quality of life (HRQoL) through 13 items. Patients rate each item on a 6-point Likert scale. The subscale scores are then combined and converted into a scale from 0 to 100. The symptom distress and HRQoL scales are inversely related: a higher symptom distress score reflects more severe symptoms, while a higher HRQoL score signifies better quality of life [25].

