## 3. Randomization and Blinding

The principal investigator, supported by a team of experienced physiotherapists with over a decade of expertise in neuromodulation and exercise therapy for UI, will oversee the implementation of the treatment protocol. Stratified randomization will be employed to ensure that the groups being compared are balanced in terms the specific levels of OAB-q SF [25]. The baseline OAB-q SF levels will be assessed before randomization, and the participants will be divided into two strata according to these levels, as outlined in the corresponding sections. One of the researchers will administer the interventions across all three groups, while the other will conduct the outcome assessments to maintain evaluator blinding. A block randomization design (block sizes of 4, 6, or 8) will be applied to ensure an equal number of participants in each group. To minimize the bias, the group allocation will be determined using a randomization table generated by an independent researcher using Excel. A double-blind design will be implemented to ensure objectivity.

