## 4. Sample Size

Statistical analysis was performed using a repeated measures analysis of variance (ANOVA), focusing on the primary variable, OAB-q SF. Drawing on a previous study on transcutaneous tibial nerve stimulation in women with idiopathic overactive bladder [26], the Cohen’s effect size was estimated to be 1.04. The statistical power was set at 0.80, with an alpha level of 0.05, considering the three intervention groups. Initially, 54 individuals were allocated to three groups (18 participants per group). To account for a potential 15% dropout rate during follow-up, three additional participants were added to each group, resulting in 21 participants per group and a total sample size of 63. The required sample size was calculated using G*Power software (version 3.1.9.2; Franz Faul, Universität Kiel, Kiel, Germany).

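### The written OAB-q SF scoring rule combines two subscales that run in opposite directions, gives no reversal, and leaves the single primary score unidentified

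*Protocol article*

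**What the plan says.** The protocol article defines the primary score only in section 5.2. The instrument "assesses symptom distress using 6 items and health-related quality of life (HRQoL) through 13 items", and "Patients rate each item on a 6-point Likert scale". The scoring rule follows: "The subscale scores are then combined and converted into a scale from 0 to 100". The next sentence gives the directions: "a higher symptom distress score reflects more severe symptoms, while a higher HRQoL score signifies better quality of life". The section does not mention reversing either scale, weighting them, or which end of a combined 0-100 scale is favourable.

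Two other sections use the instrument as if it gave one number. Section 4 sizes the trial "focusing on the primary variable, OAB-q SF", with one effect size of 1.04 that is not tied to a subscale. Section 3 stratifies on it: "The baseline OAB-q SF levels will be assessed before randomization, and the participants will be divided into two strata according to these levels". Neither section names a subscale.

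**The concern.** The grammatical object of the scoring sentence is the subscale scores, in the plural, and the result is one 0-100 scale. One of those scores falls with benefit and the other rises. Unless one is reversed, adding them sets a gain on one against a gain on the other, and the total has no clear direction.

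The rest of the plan needs a single number. One primary variable with one effect size, and two strata cut on one level, each require one score, and the scoring sentence is the only written route to it. At stake are the primary mean difference, its Cohen's d, the power, and what the strata separate.

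**Working it through.** The plan states no figure for this rule, so there is none to reproduce. The check applies the sentence as it reads and sizes the result.

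**Inputs from the protocol article.** Section 5.2: 6 distress items and 13 HRQoL items, scales in opposite directions. Section 4: effect size 1.04, alpha 0.05, 18 per group before dropout.

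**Assumptions not in the documents.** Each scale score S (distress) and H (HRQoL) is on 0-100. The combination is linear, with either item-count weights (6/19 and 13/19) or equal weights (1/2 and 1/2). Both subscales have the same SD and a true d of 1.04. The raw correlation r between them is -0.5 to -0.8. The test is a two-sided pairwise t-test.

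**Step 1: individual scores without reversal.** Item weights: C = (6S + 13H)/19. Equal weights: C = (S + H)/2.

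| Patient (S, H) | Item weights | Equal weights |
|---|---|---|
| Worst possible (100, 0) | 600/19 = 31.6 | 50 |
| Best possible (0, 100) | 1300/19 = 68.4 | 50 |
| Start (60, 50) | 1010/19 = 53.2 | 55 |
| 20 points better on both (40, 70) | 1150/19 = 60.5 | 55 |
| 20 better on S, 5 better on H (40, 55) | 955/19 = 50.3 | 47.5 |

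A 20-point gain on both scales appears as 140/19 = +7.4 with item weights and as 0 with equal weights. The patient in the last row improved on both scales, yet her total falls from 53.2 to 50.3 with item weights. With S replaced by 100 - S, the 20-point gain on both appears as +20 under either weighting.

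**Step 2: standardised effect without reversal.** With w_S and w_H the weights:

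d_C = 1.04 × (w_H - w_S) / sqrt(w_S² + w_H² + 2·w_S·w_H·r)

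For item weights the numerator is 1.04 × 7/19 = 0.383.

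- r = -0.5: 0.383/0.593 = 0.65
- r = -0.7: 0.383/0.515 = 0.74
- r = -0.8: 0.383/0.471 = 0.81

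For equal weights the numerator is 0, so d_C = 0 for every r in this range.

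**Step 3: power at 18 per arm.** Noncentral t with 34 degrees of freedom and noncentrality d × sqrt(18/2) = 3d.

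| Score analysed | d | Power |
|---|---|---|
| One subscale alone | 1.04 | 85.8% |
| Unreversed total, item weights, r = -0.5 | 0.65 | 46.9% |
| Same, r = -0.7 | 0.74 | 58.2% |
| Same, r = -0.8 | 0.81 | 65.9% |
| Unreversed total, equal weights | 0 | 5% |

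A weaker correlation of -0.3 gives d = 0.58 and power 39% with item weights. With distress reversed before combining, d is 1.09 to 1.20 and power about 89% to 94% for r from -0.8 to -0.5, over both weightings.

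**Step 4: the other reading.** If items are combined within each subscale and each subscale is converted to 0-100 on its own, there is no total, nothing cancels, and d stays at 1.04 on each. The plan then has two candidate primary scores, and sections 3 and 4 do not say which one they mean.

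**The case against.** A reader might infer that the primary outcome is mis-scored as a matter of fact. The documents do not support that. The sentence after the scoring rule interprets two separate scores, each with its own direction, and gives none for a total. That fits loose wording for combining items within each scale. Section 5.3.1 shows how the article writes when it wants a total: for the I-QOL it names an overall score beside the subscales and labels both ends. Section 5.2 does neither. Silence on reversal in a condensed article is also not a statement that none is done. These points stand, and they make the loss conditional.

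The order of operations matters too. The sentence combines first and converts second, and the direction of the raw item ratings is not stated. If all raw items ran the same way, combining them before conversion would cancel nothing. The opposite directions are stated for the scale scores, and the calculation above applies to those. This also stands.

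Two further inferences fail. Cancellation is complete only with equal weights, which the plan does not mention. And the unreversed total does span 0-100, since (0, 0) gives 0 and (100, 100) gives 100. What is compressed is the distance from the worst to the best patient, 31.6 to 68.4 with item weights.

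Finally, sections 3 and 4 may use the instrument's name as shorthand. That is possible, but shorthand for an instrument with two scores still leaves the primary score unidentified.

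**Conclusion.** The point holds as a defect in a stated rule. The only scoring sentence for the primary outcome combines two scale scores of opposite direction and gives no reversal, weights or direction for the result, while the plan treats OAB-q SF as one variable.

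If the scale scores are combined as the sentence reads, a 20-point gain on both shows as about +7.4 or 0. Pairwise power at 18 per arm then drops from about 86% to about 47-66% with item weights, or to 5% with equal weights. These power figures rest on the assumed weights, correlation, equal SDs and equal d. They use a pairwise t-test, not the planned mixed ANOVA with Tukey's correction, so they show the scale of the risk and do not forecast this trial's power.

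If separate subscale scores were meant, nothing is lost to cancellation. The sentence is then wrong as written, and the choice between symptom distress and HRQoL as primary is still open. Both readings need the same correction.

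**What to change.** In section 5.2, replace the scoring sentence with: *Each subscale is summed and converted separately to 0-100; the two subscale scores are not combined.* Then name one subscale as the primary variable and use that name in section 3 (stratification), section 4 (sample size, stating which score the 1.04 refers to) and section 8.2.2 (analysis).

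If a total is intended, state that symptom distress is reversed (100 minus the score) before combining, give the weights, and say that higher means better.

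Make the choice before anyone sees outcome data by group, so that distress, HRQoL and a total are not open to selection afterwards. Section 2.1 gives a start date of 4 March 2025. If allocation is already under way, section 3 should record which score formed the strata.

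The cost is one sentence in section 5.2, a few matching words elsewhere and a check of the scoring program. It needs no new data and no extra patients.

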### 5.3. Secondary Outcomes

#### 5.3.1. Mapping of Incontinence Quality of Life (I-QOL)

The I-QOL is a prevalent self-assessment tool for evaluating health-related quality of life in people with urinary incontinence (UI). It includes 22 questions, each scored on a 5-point scale, where 1 = extremely, 2 = quite a bit, 3 = moderately, 4 = a little, and 5 = not at all [40]. These questions are divided into three categories. The sections on Avoidance and Limiting Behaviors consist of 8 questions, Psychosocial Impacts include 9 questions, and Social Embarrassment comprises 5 questions. To calculate the overall I-QOL and subscale scores, the raw item scores are summed and then converted into a 100-point scale, where 0 represents the most severe issues and 100 indicates no problems [41]. This tool has been widely utilized and effectively validated in individuals with UI [42].

#### 5.3.2. Bladder Diary

The bladder diary is a non-invasive assessment tool that provides valuable information about bladder function. It is commonly used to evaluate the frequency and severity of symptoms associated with voiding disorders, such as overactive bladder (OAB) [43]. Additionally, it serves as a method for modifying and improving bladder health habits. Participants complete the diary over a period of 3 to 4 days per week, documenting events continuously for 24 h each day, from morning to night. The records include details of any voiding episodes, the daily fluid intake, and the activities being performed at the time [44].

#### 5.3.3. International Consultation of Incontinence Questionnaire—Urinary Incontinence Short Form (ICIQ-UI-SF)

The ICIQ-UI-SF includes three components that assess subjective frequency, subjective severity, and quality of life through a self-administered questionnaire. Questions 3 to 5 are scored items, with the responses totaled to achieve a minimum score of 0 and maximum of 21 [45].

#### 5.3.4. Electromyography (EMG)

EMG serves as a significant option for monitoring resting muscle tone, muscle strength, and endurance, as well as assessing both typical and atypical functions of the PFM. It is recognized as a reliable and objective technique for muscle evaluation that ensures patient safety [46]. EMG measures the electrical activity generated by the depolarization of muscle fibers and captures changes in the voltage over time. Measurements will be taken multiple times in both the supine and standing positions. Assessments will be carried out with the legs bent and slightly apart. The vaginal probe will be positioned so that the cord points directly forward. Participants will be instructed verbally to contract their PFM with maximum effort, using the following cue: “as if trying to prevent the release of gas.” Each evaluation session will include three sets of contractions, alternating between a 10 s contraction period and a 10 s rest period. Visible muscle activity in the hip adductors, rectus abdominis, or gluteal areas will not be allowed [47].

#### 5.3.5. Oxford Scale

The Oxford Scale is a subjective classification system used to assess the strength and quality of PFM contractions through intracavitary palpation with one or two fingers. The modified scale includes 5 grades: 0 = no contraction; 1 = flickering muscle movements; 2 = weak contraction; 3 = increased pressure with slight muscle elevation; 4 = firm contraction with moderate elevation of the vaginal posterior wall; and 5 = strong contraction with finger resistance against the abdominal wall [48].

#### 5.3.6. Tampa Scale 11 (TSK-11)

Kinesiophobia is characterized as “an excessive, irrational, and debilitating fear of physical movement and activity stemming from a sense of vulnerability to a painful injury or re-injury,” and it is particularly relevant to individuals with chronic pain who fear movement [49,50]. The TSK is a self-report scale designed to measure fear related to movement. Initially, the scale had 17 items, but the most commonly used version is now the 11-item TSK-11 [51]. Each item is scored on a 4-point Likert scale, ranging from 1 (“strongly disagree”) to 4 (“strongly agree”). The total score ranges from 11 to 44, with higher scores indicating a greater fear of movement-related injuries [52]. Assessing kinesiophobia is crucial because physical exercise plays a vital role in rehabilitation, and high levels of kinesiophobia can hinder treatment adherence [53]. Furthermore, the scale has demonstrated strong psychometric properties, with a reliability coefficient of 0.84 and a 90% confidence interval [52].

#### 5.3.7. Pain Catastrophizing Scale (PCS)

In this study, the Spanish adaptation of the Pain Catastrophizing Scale (PCS) will be utilized to evaluate pain catastrophizing. The PCS is a self-report instrument designed to measure catastrophic thoughts related to pain. It consists of 13 items that are categorized into three domains: rumination, magnification, and helplessness. Each item is rated on a scale from 0 (not at all) to 4 (all the time), with a total possible score ranging from 0 to 52 [54]. This version has demonstrated strong psychometric properties, including a Cronbach’s alpha (α) of 0.95 and test–retest reliability coefficients of 0.75 over six weeks and 0.70 over ten weeks [55]. The validated Spanish version will be used in this research.

## 6. Program Feasibility and Safety: Attendance and Compliance

Adherence to exercise regimens for UI presents a multifaceted challenge, necessitating both behavioral modification and active patient engagement [56]. The process of behavioral change, essential for effective treatment adherence, is often intricate [57]. Empirical evidence indicates that home-based interventions are less efficacious compared to those supervised by a physiotherapist with specialized training [58]. Specifically, a structured exercise program for UI, when supervised during the treatment phase, is associated with higher adherence rates in both the short and long term [59]. Moreover, non-adherence to treatment poses a significant barrier to the success of UI interventions, with the efficacy potentially diminishing substantially if compliance falls below 80% [60]. Consequently, adherence is a critical determinant of the treatment efficacy and the enhancement of quality of life [61]. This study will implement an exercise regimen aimed at enhancing core stabilization and overall strength by incorporating forced exhalation to activate the transverse abdominal muscle, thereby mitigating the adverse effects of increased intra-abdominal pressure. In both the intervention and placebo groups, the training program will be conducted under direct supervision following posterior tibial nerve neuromodulation. Participants in the exercise groups will adhere to the prescribed training frequency, as monitored by the SIRAS scale [59].

## 7. Oversight and Monitoring

This study was collaboratively designed by researchers [name] and [name], with the participation of a third researcher, [name], who will also contribute to its execution. Together, they will be responsible for coordinating patient participation, administering treatments, and monitoring adverse events or protocol deviations. Both the participants and the therapists will be instructed to promptly report any adverse events, discomfort, or deviations from the protocol. All incidents will be documented and reviewed by the research team. In the case of any serious adverse events, the principal investigators will immediately inform the Research Ethics Committee of the Catholic University of Valencia. Continuous patient monitoring will be implemented throughout the study to ensure the timely identification and management of potential risks.

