## Abstract

**Introduction:** Overactive bladder (OAB) and urinary incontinence (UI) are prevalent, particularly in older adults, and affect quality of life. OAB involves urgency, frequency, nocturia, and urgency incontinence, often linked to involuntary detrusor contractions. Treatment guidelines recommend a stepwise approach, starting with pelvic floor muscle training (PFMT), followed by pharmacological or minimally invasive therapies, such as neuromodulation. However, the combined effects of PFMT and neuromodulation have not been well established. This study aimed to evaluate the impact of combining pelvic floor exercises with neuromodulation versus PFMT with sham neuromodulation or standard physiotherapy after a 12-week intervention in individuals with OAB and UI. **Methods/Materials:** A double-blind, randomized controlled trial was designed with three groups: PFMT + neuromodulation, PFMT + sham, and conventional physiotherapy (control) in a 1:1:1 ratio. This study followed the CONSORT guidelines and was registered at ClinicalTrials.gov (NCT06783374). The sample size was calculated using GPower^®^ software, assuming a Cohen’s effect size of 1.04, a power of 0.80, an alpha of 0.05, and a 15% dropout rate, totaling 63 participants (21 per group). Participants attended 24 sessions over 12 weeks (2 sessions per week). The interventions were based on previously validated protocols. **Outcomes:** The primary outcomes included health-related quality of life, pelvic floor muscle function, pain, adherence, and general health. The secondary outcomes included Incontinence Quality of Life questionnaire, 3-day bladder diary, International Consultation on Incontinence Questionnaire–Urinary Incontinence Short Form, kinesiophobia, and electromyographic data.

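### The researchers who coordinate participants also give the treatments, and the block sizes are printed, so the next allocation could be guessed better than chance

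*Protocol article*

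**What the plan says.** All references are to the protocol article.

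- **Roles, section 7.** Of the three researchers it says: "Together, they will be responsible for coordinating patient participation, administering treatments, and monitoring adverse events or protocol deviations".
- **Roles, section 3.** "One of the researchers will administer the interventions across all three groups, while the other will conduct the outcome assessments to maintain evaluator blinding".
- **Sequence, section 3.** "the group allocation will be determined using a randomization table generated by an independent researcher using Excel".
- **Blocks and strata, section 3.** "A block randomization design (block sizes of 4, 6, or 8) will be applied to ensure an equal number of participants in each group". Baseline OAB-q SF sets the stratum: "the participants will be divided into two strata according to these levels".
- **Ratio, Abstract.** "PFMT + neuromodulation, PFMT + sham, and conventional physiotherapy (control) in a 1:1:1 ratio".
- **Order of steps.** Section 3 measures baseline OAB-q SF before randomization. Section 2.4 places all four data collections, baseline included, after the groups have been assigned.

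The article does not name who screens or enrols women, who holds the table, or how an assignment is released.

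**The concern.** Having the list made independently protects how it is produced. It does not stop someone who has watched the allocations build up within a stratum from predicting the next one. The treating researcher gives real needling, sham needling or conventional physiotherapy, so cannot avoid knowing the arm. Section 7 places that person in a team that also coordinates participants, and the block sizes are in print.

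There is room for judgement at entry. Section 2.2 requires women to be able to keep up an exercise regimen, and section 2.3 excludes serious medical conditions without defining them. The arms differ in demand: section 4.1.1 describes 90-minute multi-block sessions (section 2.4 says about 60 minutes for everyone), while section 4.1.3 describes control sessions of 20 to 40 minutes. Section 6 treats adherence as decisive for efficacy. A team member who expects an exercise slot next has a reason, perhaps unconscious, to prefer a fit and motivated woman for it.

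Stratifying on OAB-q SF does not balance motivation, fitness or expectation. The primary outcome in section 5.2 is self-administered, so such differences could carry straight into it. The trial does not plan to measure motivation or expectation, so adjustment could not reliably repair the imbalance.

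**Working it through.** The article gives no figure for predictability, so there is none to reproduce.

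**Inputs from the article:** three arms at 1:1:1 (Abstract), block sizes 4, 6 or 8 and two strata (section 3), 63 participants (section 4).

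**Assumptions:** the guesser knows all past allocations in the stratum and the set of block sizes; the strata hold 32 and 31 women.

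**1. Which sizes fit three arms.** The remainders on division by 3 are 1 for size 4, 0 for size 6 and 2 for size 8. Only 6 gives 1:1:1 within each block.

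**2. Every block a known 6, two places per arm.** The chance that the best guess is right equals the expected share of the commonest remaining arm:

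- Place 1: 2/6 = 0.333
- Place 2: 2/5 = 0.400
- Place 3: 2/4 = 0.500, whichever two were drawn
- Place 4: three places remain. They include a pair in 12 of 20 cases, so 0.6 × 2/3 + 0.4 × 1/3 = 0.533
- Place 5: two places remain. They match in 3 of 15 cases, so 0.2 × 1 + 0.8 × 0.5 = 0.600
- Place 6: 1.000

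The sum is 3.367, and 3.367/6 = 56.1%. The next arm is certain at place 6 always and at place 5 with probability 0.2, which is 1.2 of 6, or 20% (12.6 of 63).

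With strata of 32 and 31 there are ten complete blocks, plus part blocks of 2 and 1. Certain: 10 × 1.2 = 12 of 63 = 19.0%. Best guess right: (10 × 3.367 + 0.333 + 0.400 + 0.333)/63 = 34.7/63 = 55.1%.

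**3. Sizes drawn at random.** After each allocation the guesser updates the probability of each block size and position. The chance that the next arm is *a* is the sum, over those states, of the state's probability times (places left for *a*)/(places left in the block). Sizes are equally likely. In blocks of 4 and 8 the leftover places go to different arms chosen at random, which is an assumption because the article does not say. Results from 500 simulated trials:

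| Blocks | Next arm certain | Best guess right |
|---|---|---|
| 6 only | 19.0% | 55.2% |
| 4, 6, 8 mixed | 0.5% (about 0.3 of 63) | 50.0% |
| 3, 6, 9 mixed | 3.3% (about 2 of 63) | 54.2% |
| Chance | 0% | 33.3% |

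The first row agrees with the hand calculation. Mixing sizes removes nearly all certainty but little of the guessing advantage. Changing to multiples of three does not remove it either, so this point is separate from the divisibility of the block sizes.

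**The case against.** The strongest reply is that control of entry is an inference. Section 7 speaks of coordinating participation, which could mean scheduling and follow-up. Section 2.2 describes recruitment by flyers, social media, health centres and specialist referral. Section 3 keeps the outcome assessor blinded, and if that person admits women the route closes. This stands as a limit: the point is conditional on overlap between entry and knowledge of past arms. It does not dispose of the point, because section 7 gives coordination and treatment to the three jointly, assigns entry to nobody else, and sits awkwardly with the divided roles in section 3.

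A second reply is that a condensed article may leave concealment to the full protocol. That is right, and the missing release procedure is not in itself the fault. The weakness lies in the stated combination of joint roles, one therapist for all arms and printed block sizes.

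Two stronger readings are tempting. A reader might infer that the team can simply look up the next assignment, so that all allocations are known. Nothing supports this: the article says only that an independent researcher generates the table, and does not give it to the team. A reader might also take 20% certainty as the size of the problem. That needs a known, fixed block of 6, and section 3 lists three sizes without saying whether one is chosen or they vary.

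**Conclusion.** The point holds in conditional form. If someone who knows past allocations also influences when or whether a woman enters, the next arm can be guessed correctly about 50% to 56% of the time, against 33% by chance. Certainty runs from about 20% with a known block of 6 down to about 0.5% to 3% with randomly mixed sizes. For most women foresight is therefore probabilistic. The figures rest on full tracking of past allocations within stratum, known block sizes and, for sizes 4 and 8, an assumed way of filling the blocks.

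The calculation measures the opportunity for selection. It does not show that selection will occur, nor how far it would move the OAB-q SF comparison. The change is worth making because it is cheap and the bias, if it arose, could not be reliably corrected afterwards.

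**What to change.** 1. The independent researcher who generates the table also keeps it, with no access for the three researchers.
2. That researcher replaces the printed block sizes with randomly varying multiples of three, not disclosed to the three researchers. Withholding the current sizes cannot work, because they are published and these researchers helped design the study.
3. Each assignment is released individually, only after consent, baseline OAB-q SF and stratum have been logged.
4. Eligibility is confirmed by a team member who neither treats patients nor sees past allocations, such as the blinded assessor. This step matters most, since the 3, 6, 9 result shows that new sizes alone leave much of the guessing advantage if they become known.
5. Sections 3 and 7 are reconciled on who treats, who assesses and who admits. Sections 2.4 and 3 are reconciled on whether baseline comes before assignment.

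The cost is one message and a short wait for each of 63 participants, a simple release log, and some added work for whoever confirms eligibility. If such a procedure already exists in the full protocol, a sentence stating it would settle the release step. The block sizes and roles would still need attention.
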